### Data management

Study data will be stored in REDCap (https://www.project-redcap.org/), using the in-built quality control functionality including data range and consistency checks.

### Confidentiality

All data will be collected with informed consent except where a waiver has been provided by the relevant Ethics Committees. All written materials will be securely stored in a locked office with authorised access only. Data will be stored for at least 15 years as per the National Health Medical Research Council (NHMRC) Guidelines [27].

### Statistical methods

The study’s data will be stored and managed in REDCap, data will be exported for analysis. A range of descriptive statistics will be presented (means and standard deviations; medians and interquartile ranges; counts and percentages) for each site individual and for the full sample, alongside figures if appropriate, which provides a basic overview of the study data. Analysis to address the study’s primary research question will utilise a mixed model framework; here, the outcome will be the absolute PC-QoL score, and the difference between the “nil-intervention” and the “post-intervention” groups will be determined with a 2-level fixed term in the model. The coefficient for this term (and 95% confidence interval) from the model will be reported, as this will represent a ‘whole of program’ effect. The within-site clustering will be controlled for, in the model, by including both a fixed and random term for the study site; if individual participants present during more than one observation periods, this will also be controlled for using a random term in the model. Numerous covariates have been considered for in the modelling, those that will be included (and their justification) are as follows: age, sex and calendar week (to control for risk differences by age, sex and time/seasonal effects respectively). It has been demonstrated that including covariates, such as those listed, typically increases study power [28]. The appropriateness of the model, and the validity of the relevant assumptions, will be assessed using both model fit statistics and through the examination of residual plots. If the final selected model deviates from that described above, justification to support the change will be provided in the report.

Further to the primary analysis outlined above, both a minimally adjusted model (following a similar modelling framework and structure, but with no covariates included the model) and a completely unadjusted model (a Student’s t-test) will be reported. Secondary outcomes (for example, cough presence, quality and duration and management) will initially be assessed using basic comparisons, for example, Chi-squared tests and Student’s t-tests. A mixed model framework (as used in the primary analysis) will be used to quantify the effect of the intervention on prognostic factors of interest (logistic regression for binary outcomes, Poisson regression for count outcomes; with 95% confidence intervals reported alongside effect estimates). The focus of all analysis will be on reporting the effect size estimates (with confidence intervals), as opposed to focusing on statistical significance.

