#### Criteria for discontinuing or modifying allocated interventions

Program implementation will use a combined decolonising research approach [14] that includes Participatory Action Research (PAR) [13] and consideration of barriers and facilitators identified with the Consolidated Framework for Implementation Research (CFIR). As well, context-sensitive adjustments of implementation processes that engage with First Nations consumer views to ensure meaningful partnerships, consultation, effectiveness, and sustainability, will be used. Identification of adaptations required to implement program core components will involve interviews and focus groups with stakeholders, including:

Parents: Purposive sampling with both criterion and snowball sampling [19] to initially recruit parents of First Nations children with recurrent respiratory infections and/or cough, and then more broadly the wider First Nations parent community. At all interviews with First Nations participants, a First Nations researcher will be present.Healthcare providers (HCP): Recruitment of HCPs at the local primary care clinic who are involved in caring for First Nations children. Snowball sampling will be used to ensure wider relevant stakeholders are consulted.

Inclusion criteria of participants for interviews:

Parents or carers of First Nations children in the town/community: The pragmatic definition of parents include grandparents, aunts and uncles, foster parents, or other family members within the kinship system, who take on the responsibility of taking care of a child.HCP: Any HCPs within the local clinic who are involved in the medical care of First Nations children, including but not limited to doctors (paediatricians, service coordinators, Aboriginal health practitioners, primary-care liaison personnel), nurses and clerks.External stakeholders: such as Aboriginal Community Controlled Health Councils, peak bodies, hospital HCPs such as paediatricians, nurses, and physiotherapists.

The interviews and focus groups provide insights to understand local knowledge and perspectives of chronic wet cough and the barriers and facilitators to implementing the program. Researchers with qualitative research skills and content experts (clinician or Aboriginal lead depending on participant) will conduct interviews and focus groups. Interview participants will be recruited during the “nil-intervention” period, prior to the implementation of the program.

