**Health: Cough-specific Quality of Life (PC-QoL)**
The primary outcome will be the parent-proxy Cough-specific Quality of Life [23] (PC-QoL) (8-question version) for children with chronic wet cough. Effective management of children with chronic wet cough by clinicians will be assessed by measuring PC-QoL between 6-weeks to 3-months after presenting to the local clinic. The PC-QOL tool is a valid, reliable, and responsive tool for measuring the burden of chronic cough in children [23] and has been used effectively in First Nations settings [9].Rationale: Children with chronic wet cough in the absence of alternative causes are likely to have protracted bacterial bronchitis that should resolve if managed with an appropriate antibiotic. Hence, if children receive an appropriate antibiotic, then we expect they will have improved quality of life after 6-weeks to 3-months compared to those who did not.The PC-QoL scores will be compared nil- and post-intervention in different children who presented to the clinic with a chronic wet cough. A value of 0.9 is the calculated minimum important difference in PC-QOL to demonstrate a clinically significant improvement [23].

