### Recruitment

#### Recruitment for QOL survey in nil-intervention and post-intervention groups

Participants will be recruited following a medical record audit identifying children who presented for chronic wet cough or who had multiple presentations for cough and chronic wet cough. This will be subsequently confirmed through parental history from interviews conducted by two researchers (including at least one specialist clinician). Children will be excluded if they are non-First Nations, if they do not have a chronic wet cough (i.e., a daily wet cough ≥ four-weeks) or if the family is unable or unwilling to give informed consent (Fig. 2).

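### The primary model does not allow for several children rated by one carer, so its interval would be wrong, in a direction not known in advance, if siblings are enrolled

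*Protocol article*

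**What the plan says.** On the outcome (Outcomes, Health: Cough-specific Quality of Life): "The primary outcome will be the parent-proxy Cough-specific Quality of Life". The score is therefore given by the carer. The contrast is mainly between different children: "The PC-QoL scores will be compared nil- and post-intervention in different children who presented to the clinic with a chronic wet cough".

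On dependence (Statistical methods): "The within-site clustering will be controlled for, in the model, by including both a fixed and random term for the study site". The only other random term is for a repeat child: "if individual participants present during more than one observation periods, this will also be controlled for using a random term in the model". No carer, family or household term is named. The section leaves some room to change: "If the final selected model deviates from that described above, justification to support the change will be provided in the report".

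On recruitment (Recruitment for QOL survey): "Participants will be recruited following a medical record audit identifying children who presented for chronic wet cough", followed by confirmation from the parent's history. The exclusions are children who are not First Nations, children without chronic wet cough, and the case "if the family is unable or unwilling to give informed consent". Nothing there limits enrolment to one child per family. Eligibility for the clinician-management assessment, which the PC-QoL serves, runs from 0 to 17 years, so siblings can both qualify. Pragmatic data collection describes a limited pool of diagnosed patients and an aim of 12 children per cluster per stage.

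**The concern.** Two children scored by one carer share the rater and often the household. Their scores are likely to be positively correlated beyond what site explains. The repeat-child term does not capture this, because siblings are different participants. The site term captures only what is common to the whole site.

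The standard error of the single primary coefficient would therefore rest on a wrong count of independent pieces of information. The article says its analyses will focus on effect estimates with confidence intervals rather than on significance, so the width of this interval is a main product of the trial. With about 12 children per cluster per stage, a handful of carers with two children is enough to move it.

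**Working it through.** **Step 1: the plan's own figures.** Inputs from Sample size: SD 1.3, differences 1.6 and 0.9, COV of cluster size 0.65, ICC 0.01, alpha 0.05, four clusters.

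- Per site, 12 per period, difference 1.6, two-sided t-test: power 82.1% (stated as above 80%).
- Whole study, m children per cluster per period: design effect = 1 + ((1 + COV²)m − 1) × ICC.
  - m = 5: 1 + (1.4225 × 5 − 1) × 0.01 = 1.061. Effective n per period = 20/1.061 = 18.8. Power for 1.6 is 95.7% with t (96.5% normal), stated as above 95%.
  - m = 10: 1 + (1.4225 × 10 − 1) × 0.01 = 1.132. Effective n per period = 40/1.132 = 35.3. Power for 0.9 is 82.0% with t (82.9% normal), stated as above 80%.

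All three stated figures reproduce. They assume no sibling correlation.

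**Step 2: effect of siblings on the variance.** Let n be the children per period, s the share of children who are in a sibling pair, and ρ the correlation between two scores from one carer, given site.

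- Pairs in the same period: there are ns/2 pairs per period, so the variance of a period mean is (SD²/n)(1 + sρ). The variance of the nil/post difference is multiplied by 1 + sρ.
- Pairs split across periods: there are ns pairs, so the covariance of the two means is SD² × sρ/n. The variance of the difference is multiplied by 1 − sρ.
- A mixture multiplies it by 1 + ρ × (same-stage share − split share), which can be close to 1.

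**Step 3: numbers.** The document gives neither s nor ρ. Assumed ranges: s from 5% to 40%, ρ from 0.3 to 0.7. Ratio = correct interval width divided by the model's width = √(1 ± sρ). Coverage of the nominal 95% interval = 2Φ(1.96/ratio) − 1.

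| s | ρ | Same stage: ratio | Coverage | Split: ratio | Coverage |
|---|---|---|---|---|---|
| 5% | 0.3 | √1.015 = 1.01 | 94.8% | √0.985 = 0.99 | 95.2% |
| 20% | 0.5 | √1.10 = 1.05 | 93.8% | √0.90 = 0.95 | 96.1% |
| 40% | 0.7 | √1.28 = 1.13 | 91.7% | √0.72 = 0.85 | 97.9% |

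**Step 4: on the PC-QoL scale.** With 4 × 12 = 48 children per period, the half-width that ignores siblings is 1.96 × 1.3 × √(2/48) = 0.52 points. At s = 20% (about 10 of 48 children, or five pairs per stage) and ρ = 0.5, the correct half-width is 0.52 × 1.05 = 0.55 for same-stage pairs, or 0.52 × 0.95 = 0.49 for split pairs.

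**The case against.** The strongest reply is that this is an omission with no demonstrated consequence. Nothing in the article says that siblings will be enrolled or how many are expected. A rule of one child per family, or a further model level, could stand in a full protocol or analysis plan that is not shown, and the article allows a justified change of model. At modest sibling shares the interval moves by a few percent, which is small against differences of 0.9 and 1.6. This stands as a limit on the size of the point. It does not remove the point, because the article names its random terms explicitly and those terms leave out the carer.

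Three stronger readings are tempting, and the document supports none of them.

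- A reader might infer that the interval is simply too narrow. That needs siblings to fall mainly in the same stage. The recruitment window of 6 weeks to 3 months after presentation, and the 3-month implementation period between stages, make this plausible for siblings who cough together. No text shows it, and a family with one child in each stage is equally compatible with the design.
- A reader might take the kinship wording, "The pragmatic definition of parents include grandparents, aunts and uncles, foster parents, or other family members within the kinship system", as defining who completes the PC-QoL. It stands among the inclusion criteria for the qualitative interviews. If it did apply, siblings might also have different raters, which would weaken the shared-rater argument.
- A reader might infer that the sample size is inadequate. The stated power reproduces, and the section presents it as guidance for design. The target of 12 per cluster per stage also exceeds the 10 used for the 0.9 difference.

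**Conclusion.** The point holds conditionally. As written, the primary model treats children rated by one carer as independent given site, and nothing stated in recruitment prevents such children from being enrolled. If they are, the interval for the nil/post coefficient is wrong: by about 1–13% too narrow relative to its stated width for same-stage pairs, or about 1–15% too wide for split pairs, with partial cancellation in a mixture. These figures rest on assumed sibling shares of 5–40% in pairs and within-carer correlations of 0.3–0.7, because the document gives neither. This is a minor weakness of a specified model with a cheap remedy. It does not show that the trial's inference will fail.

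**What to change.** Add to REDCap a carer/household code for each child with a PC-QoL score. Include it as a random term in the primary model, alongside the site and repeat-child terms. State in advance that, if the term cannot be estimated, standard errors clustered on carer will be used. Report the number of carers as well as children per stage. This corrects the interval whichever way siblings fall.

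The cost is one coded field and one model term. The term may be estimated at zero if few siblings enrol, in which case the result is almost unchanged. The interval may widen slightly if same-stage siblings are common. Recruitment has already begun and the stored data are de-identified, so the code is best captured now; the link may be hard to recover later.

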### Interim analyses

No interim analysis is planned.

### Methods in analysis to handle non-adherence to the protocol and statistical methods to handle missing data

Data audits will be completed to query missing entries. Unvalidated data will be excluded from analyses. The study team will regularly verify information that has been collected and monitor for missing data or errors in data entry.

### Oversight and monitoring

#### Steering committee

The APPLE Study Steering Committee, comprised of the Coordinating Principal Investigator, Principal Investigators, and invited collaborators and stakeholders will assume responsibility for the APPLE study design and implementation.

#### Executive committee

The APPLE Study Executive Committee will meet regularly to oversee the day-to-day management of the APPLE study. It will be comprised of key study members and report to the Steering Committee. Day-to-day decisions will be made on minor issues without the need for prior approval. The Executive Committee will ensure decisions made by the Steering Committee are communicated to the Operations Group.

### Operations group

The APPLE Operations Group, comprising the Coordinating Principal Investigator, Study Manager, and selected study staff, will operationalize decisions made by the Steering Committee. The Operations Group will also have oversight of study procedures.

### Consumer reference group

A consumer reference group will advise on study process and receive updates on study progress. The group will include parents and family member whose First Nations child/children have lived experience of chronic lung disease.

### Plans for communicating important protocol amendments to relevant parties (e.g., ethical committees)

Protocol amendments will be documented and submitted to the relevant research ethics and governance committees.

### Dissemination plans

Results of this study will be published and presented in a variety of formats, including presentations at relevant medical conferences and published in peer-reviewed journals. A final report will be disseminated at the conclusion of the study to participating families, consumer reference groups, participating medical clinics as well as to local councils and peak bodies.

## Discussion

Despite massive investment by government, the health gap between First Nations and other Australians is still large and not closing rapidly [29]. Many diverse health conditions contribute to the health gap [30] and only by addressing each of these conditions and the underlying contributing factors will the gap be closed. Respiratory disease contributes significantly to the health gap and PBB, if left untreated, can progress to chronic irreversible and life-limiting respiratory disease, is highly prevalent in children in some First Nation populations [31, 32]. Approaches to address health problems in First Nations have traditionally focused on communities and on health systems separately. We propose an approach that targets families and health systems simultaneously. Our previous research has shown that families are often not aware that chronic wet cough in children is a symptom that requires medical attention [8, 9]. Concurrently, help-seeking by families is futile if the attending clinician is not proficient in managing the condition requiring treatment. As PBB was only formally recognised in 2006 [33], clinicians are often still uninformed about correct screening and management [5]. We hypothesise that a tailored intervention, based on identified barriers and facilitators identified through engagement with carers and health service providers, will result in improved health-seeking by carers of children with chronic wet cough and better management of chronic wet cough by clinicians. We expect this to result in improve lung health children seeking help for chronic wet cough.

### Rationale for our chosen approach

We aim to simultaneously 1) change the help-seeking of parents and 2) clinician practice to 3) improve the health of children with PBB. Initiatives by external agencies in First Nations settings have traditionally been hampered by the lack of involvement of First Nations people [34]. In contrast, our study is a partnership with local First Nations communities. PAR approaches, which have been demonstrated to be effective in First Nation settings [35] will be used in the study. The PAR approach facilitates community empowerment and translation of research into action.

To influence clinician practice, we will use an implementation science approach grounded in the CFIR. The CFIR is among the most comprehensive and widely used frameworks in implementation science [36], which considers a wide range of determinants that have been found to influence implementation outcomes. These determinants will be considered when adapting and individualising the program to site-specific contexts.

A pseudo-randomised stepped wedge trial will be used, with no formal randomisation, because we have already commenced this study, and timing of the intervention will vary significantly between study sites/clusters due to the considerable number of hurdles that must be overcome at each study site before the study can commence. Such hurdles include challenges with accessing remote communities where access can be impossible for extended periods due to flooding, COVID-19 related restrictions to entry by non-essential workers imposed by government, sorry business, local First Nations lore-time of which the timing varies from year-to-year and that can be imposed at short notice. Also, once the need to facilitate appropriate medical help-seeking and optimal medical management of chronic wet cough and PBB becomes clear to local stakeholders, a randomised design becomes unacceptable. The stepwise analysis of change resulting from implementation of the program will, however, provide evidence of the efficacy of the program. Replication at multiple sites will potentially further strengthen the study findings and provide an opportunity for analysis of the relative efficacy of the study intervention at different study sites.

The implementation of the program will be driven by the research team. Our study will determine if the combined PAR-implementation science approach, directed at both families and health systems, is effective across different settings. The study will also determine how the strategy should be adapted to different settings and the cost-effectiveness of our approach. If effective, the team will continue to support the program scale-up in other settings in a purveyor function, and sustainability will be supported by e-module training. The current study will provide ideas on how to automate the identification of site-specific barriers that can be addressed to improve the delivery of the program.

### Trial status

The trial has been approved by the Western Australian Aboriginal Health Ethics Committee on 26.06.2017; approved by the Child and Adolescent Health Service Ethics Committee on 28.07.2020; approved by Human Research Ethics Committee of the Northern Territory Department of Health and Menzies School of Health Research on 23.03.2021; approved by University of Queensland's Human Research Ethics Committee on 09.11.2020. Recruitment has commenced.

## Data Availability

The datasets used and/or analysed during the current study available from the corresponding author on reasonable request.

## Abbreviations

PBB: Protracted bacterial bronchitis
STaRI: Standards for Reporting Implementation Research
COREQ: The Consolidated Criteria for Reporting Qualitative research [14]
NHMRC: National Health Medical Research Council
PC-QoL: Parent proxy Cough-related Quality of Life
HCP: Health Care Provider
CFIR: Consolidate Framework for Implementation Research
REDCap: Research Electronic Data Capture
